### Sample size

Calculating sample sizes for interrupted time series analyses is often done pragmatically. Per recommended methodological standards, the study will include 12 time periods (monthly repeated measures) before and after the introduction of the educational intervention, each time period providing far more than the recommended 50–100 cardiac arrest cases per month [45, 46]. Based on the estimated 6000–7000 cardiac arrest cases available per year (with 12,000–14,000 cases in total in the study), from the proposed regions, there will be an estimated 500 cardiac arrest cases and 50 survivors per month for each of the time units in the before and after time periods.

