### Setting

This study will take place in 10 sites/ambulance Communication Centres distributed in 5 Canadian provinces/regions. They are all associated with sophisticated high-performing paramedic services and receiving hospitals already providing OHCA outcomes data to the CanROC network. Together, these 10 ambulance Communication Centres provide services to an estimated population of 13,919,809 [range 107,406 – 4,800,000], see Table 1. They process more than 1,725,000 9–1-1 calls per year, approximately 8312 of which are for eligible non-traumatic OHCA for which resuscitation is attempted. These sites have also been selected because their ambulance telecommunicators have various training backgrounds, and utilize various types of systems/platforms. All the selected Communication Centres have been providing telecommunication-assisted CPR instructions since or before April, 2004. Our research group has a decade-long history of collaboration with most of these partners. They have all provided a letter in support of this proposed project.

**Table 1 Tab1:** Annual 9–1-1 call volume, with sudden cardiac death distribution, per study site catchment area

Province	Community	Catchment Population	9–1-1 calls/year	Eligible SCD cases/year
British Columbia	Entire Province	4,800,000	600,000	2800
Alberta	Edmonton	4,100,000	600,000	2400
	Calgary			
Ontario	Toronto	2,790,000	280,000	1650
	London	455,526	66,000	291
	Niagara	431,346	60,000	250
	Sudbury	161,531	14,000	134
	Thunder Bay	107,406	9000	102
Nova Scotia	Entire Province	1,000,000	84,000	585
PEI	Entire Province	146,000	12,000	100
	Total	13,991,809	1,725,000	8312

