### Data analysis

#### Overall survival to hospital discharge and community bystander CPR rates – objectives 1 and 2

Individual time series plots for each of the 5 regions will be created to visually inspect the immediate and long-term effects of the intervention, and the presence of trends, cyclical patterns, and outliers. The aggregated monthly rates in each region, expressed as percentages, will be analyzed using a simple linear segmented autoregressive model. To avoid instability due to small numerators and denominators at some sites, multiple sites within the same region will be pooled for the analysis where necessary. The model will include fixed terms for time pre-intervention, intervention, and time post-intervention. The implementation period will be censored from analysis by coding the intervention variable as missing during these months [43]. The model will be estimated using maximum likelihood estimation. Statistical significance will be obtained as the estimated beta coefficients divided by their standard errors with standard errors accounting for the autoregressive parameters. As the primary analysis will be conducted at the aggregate level, no covariates will be adjusted for in this analysis. We will assess serial autocorrelation, non-stationarity, and seasonality using the Durbin-Watson statistic, Dickey-Fuller unit root test, and visual inspection of residual plots against time. The fit of the final model will be assessed by inspecting residuals around the predicted regression lines. In case of substantial non-normality, the analysis will be conducted on the log or logit scale. The effect of the intervention will be expressed for each outcome as intercept and slope changes, where the former can be interpreted as the immediate effect of the intervention and the latter as the gradual effect of the intervention on each outcome over time. We will also evaluate the difference, at 12 months post-implementation, between the fitted post-implementation rates and the projected rates estimated using only the pre-intervention data. This represents the counterfactual effect, that is, the difference between the observed rate and the rate that would have been observed had the intervention not been implemented. We will express these differences on absolute or relative scales, with 95% confidence intervals (CI) calculated using the method of Zhang et al. [44]

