To obtain pooled estimates across all five regions, two methods will be used: First, we will use a random effects meta-analytical approach to pool the five region-specific intervention effect estimates and their standard errors. Next, we will use generalized linear mixed effects regression of the site-specific data with random intercepts for the sites and random slopes for time. All analyses will be conducted using SAS version 9.4 (SAS Institute, Inc., Cary, North Carolina).

#### Successful completion of telecommunication-assisted CPR instructions and frequency of CPR instructions leading to chest compressions in rare victims not in cardiac arrest – objective 3

We will use descriptive statistics with 95% CIs to describe successes in various stages of the implementation of CPR instructions (e.g. instructions offered, provided, completed, chest compressions initiated), and the frequency with which chest compressions are (rarely) going to be provided to a victim not in cardiac arrest.

#### Frequency and impact of agonal breathing on OHCA recognition by telecommunicators – objective 4

The frequency and impact of agonal breathing (proportion of missed OHCA as a result of agonal breathing) will be reported using kappa and descriptive statistics with 95% CI. Sensitivity, specificity, negative and positive predictive values will be computed with 95% CIs for the ability of ambulance telecommunicators to recognize OHCA over the telephone. OHCA recognition rates will be compared in the before and after periods using statistical analyses described above for Objectives 1 and 2.

#### Speed with which OHCA is recognized and telecommunication-assisted CPR instructions are initiated – objective 5

Descriptive statistics with 95% CIs will be used to describe various time delays occurring during telecommunication-assisted CPR instructions (e.g. time to OHCA recognition, to initiation, and to completion of instructions). We will compare these time intervals (continuous variable) in the before and after periods using statistical analyses similar to those described above for Objectives 1 and 2.

#### Objectives 6, 7, and 8

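### The sample-size claim of far more than 50–100 cases per month rests on an all-region total, but the primary analysis models five regional series, and Nova Scotia and PEI fall below 50

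*Protocol article*

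**What the plan says.** The Sample size section calls the sizing pragmatic and gives no power calculation. Its criterion is 12 monthly periods before and 12 after, with "each time period providing far more than the recommended 50–100 cardiac arrest cases per month". The supporting count is "Based on the estimated 6000–7000 cardiac arrest cases available per year (with 12,000–14,000 cases in total in the study), from the proposed regions", from which "there will be an estimated 500 cardiac arrest cases and 50 survivors per month for each of the time units" follows.

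The Data analysis section for objectives 1 and 2 sets the unit of modelling: "The aggregated monthly rates in each region, expressed as percentages, will be analyzed using a simple linear segmented autoregressive model". Against small counts it provides that "multiple sites within the same region will be pooled for the analysis where necessary". To combine regions, "we will use a random effects meta-analytical approach to pool the five region-specific intervention effect estimates and their standard errors"; a mixed model of site-specific data is the second method.

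The Setting section states that "This study will take place in 10 sites/ambulance Communication Centres distributed in 5 Canadian provinces/regions". In Table 1 Nova Scotia is a single province-wide row ("Nova Scotia Entire Province 1,000,000 84,000 585"), and so is PEI, with 100 eligible cases a year.

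**The concern.** The count used to show adequacy and the series that are modelled are different things. About 500 cases a month describes one national series, and no stated analysis fits such a series. The protocol will report intercept and slope changes for each region, a 12-month counterfactual difference, and analyses stratified by site. If the cited minimum is meant for the series under the model, the statement is untrue for two of the five.

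The safeguard against small denominators does not reach those two, because each has only one row in Table 1 and there is nothing within the region to pool. At stake is how the regional results are read. A flat result in PEI or Nova Scotia, or a difference between regions, could be taken as informative because the protocol says every time period is amply filled.

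**Working it through.** **Inputs.** Annual eligible cases from Table 1: British Columbia 2800; Alberta 2400; Ontario 1650 + 291 + 250 + 134 + 102 = 2427; Nova Scotia 585; PEI 100; total 8312. Annual base in the Sample size section: 6000–7000. Survival: 10% is implied by 50 survivors in 500 cases; 8% is the level that the Background says is rarely exceeded. Hypothesised gain: 5 points.

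**The protocol's own figure.** 6000/12 = 500 and 7000/12 = 583. The stated 500 reproduces only as the sum over all regions at the lower end of the range. Table 1 would give 8312/12 = 693.

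**Cases per month in each modelled series.** Table 1 figure: annual cases/12. Rescaled figure: (regional cases/8312) × 6000/12 to (regional cases/8312) × 7000/12.

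| Region | Table 1 | On 6000–7000 a year |
|---|---|---|
| British Columbia | 233 | 168–196 |
| Ontario | 202 | 146–170 |
| Alberta | 200 | 144–168 |
| Nova Scotia | 48.8 | 35–41 |
| PEI | 8.3 | 6–7 |

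Three series exceed 100 on either base. Nova Scotia and PEI are under 50 on both.

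At 10% survival PEI expects 8.33 × 0.10 = 0.8 survivors a month. The chance of a month with none is 0.9^8.33 = 42% (0.92^8.33 = 50% at 8% survival). The fallback to a log or logit scale is undefined for such a month.

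**What this means for precision.** The protocol states no power, so this is illustration. Assumptions: binomial monthly variance only, no autocorrelation, no heterogeneity between regions, months 1–12 and 14–25, Table 1 counts, two-sided 5%.

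- Monthly SE = √(p(1−p)/m), where m is cases per month.
- In ordinary least squares with intercept, time, level and post-slope terms, the SE of the level change is 0.870 × the monthly SE. The SE of the difference at month 12 after implementation is 1.665 × the monthly SE.
- Power = Φ(z − 1.96) + Φ(−z − 1.96), with z = 5/SE in points.

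Example, PEI at 10%: √(0.09/8.33) = 10.4 points; level-change SE 0.870 × 10.4 = 9.05; z = 0.55; power about 9%.

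| Series | SE level, 8% / 10% | Power, level | SE 12-month, 8% / 10% | Power, 12-month |
|---|---|---|---|---|
| Pooled, five regions | 0.90 / 0.99 | >99% | 1.72 / 1.90 | 75–83% |
| Three large regions, each | 1.55–1.67 / 1.71–1.85 | 77–90% | 2.96–3.19 / 3.27–3.53 | 29–39% |
| Nova Scotia | 3.38 / 3.74 | 26–32% | 6.47 / 7.15 | 11–12% |
| PEI | 8.18 / 9.05 | 9% | 15.7 / 17.3 | 6% |

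With a common survival rate, inverse-variance weights are proportional to cases: PEI 100/8312 = 1.2%, Nova Scotia 585/8312 = 7.0%. The three large regions alone give a level-change SE of 0.94–1.04, against 0.90–0.99 with all five.

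On 6000 cases a year (500 a month) the pooled level-change power is still about 99%, and the pooled 12-month power is 61–70%.

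**The case against.** The strongest reply is that the sentence is true of what it counts. It speaks of cases in a time period, and the next sentence shows that the base is all the proposed regions together. No adequacy is claimed for any single region. The rule comes from two cited sources that are not in the document, so its application to each modelled series is an assumption. Objective 1 concerns overall survival, the 5-point hypothesis is not regional, and stratification by site is described as exploratory.

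Much of this stands. The unit of the rule has to be labelled as an assumption. But on the reply's reading, the criterion is checked against a series that the protocol never fits, so it says nothing about the models that will be run.

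Three stronger readings are tempting and not supported:

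- *The primary result is undersized.* The two small regions carry about 8% of the pooled weight, and the pooled level change keeps ample precision under the assumptions above. Heterogeneity between regions or positive autocorrelation would reduce it, but the document gives no value for either.
- *Most sites fail the rule, so the mixed model is unsound.* London (24 a month), Niagara (21), Sudbury (11) and Thunder Bay (8.5) are indeed small. But nothing in the document applies the 50–100 rule to sites in a mixed model, whose random effects share information across sites, and Ontario's small sites can be pooled for the regional series.
- *Nova Scotia fails badly.* On Table 1 it misses 50 by 1.25 cases a month. It is clearly short only on the Sample size section's lower count.

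**Conclusion.** The concern holds in limited form. The stated adequacy is correct for the all-region total and fair for British Columbia, Alberta and Ontario. It is wrong for PEI by a wide margin, and for Nova Scotia marginally (48.8 a month on Table 1) or clearly (35–41 on the protocol's own sample-size count). This rests on two assumptions: that the cited minimum refers to the series being modelled, and that the five regions are the five provinces of Table 1. The power figures rest further on binomial variance alone and are illustrative. What is misstated is the adequacy of the regional series; the pooled level change is little affected. Severity: minor to moderate.

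**What to change.** In the Sample size section:

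1. Reconcile the 6000–7000 cases a year with the 8312 of Table 1, and state one annual base.
2. Replace the claim of far exceeding the minimum with the monthly count for each region on that base, and say that the standard is met in three of five regions.
3. State that the pooled estimate answers the 5-point survival hypothesis, and that the Nova Scotia and PEI estimates and the small-site strata are descriptive.

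Merging Nova Scotia and PEI into one series is not a dependable remedy. Together they reach 685/12 = 57 a month on Table 1, but only 41–48 on 6000–7000 a year, and a planned regional estimate would be lost.

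The cost is one rewritten paragraph with less favourable figures. No extra patients, data or analyses are needed.

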## Discussion

The proposed research study will improve clinical care and outcomes for cardiac arrest victims, use various knowledge translation strategies to engage potential bystander CPR providers, engage 9–1-1 telecommunication officers in research activities, develop new research centers of excellence among Canadian ambulance Communication Centers, expand CanROC’s research network and capabilities, and create new commercial technology (IBM-Watson collaboration). We estimate absolute bystander CPR and survival rates could increase by 20 and 10% respectively, after the completion of the entire research program. Given the reported incidence of sudden cardiac death in Canada (35,000/year), we could save as many as 3500 victims/year, positively impact their families, decrease health care burden, and return active members of society to a productive life.

## Data Availability

Data produced in the study may be accessible via the corresponding author upon reasonable request and after review by a data access committee.

## Abbreviations

AHRC: Applied Health Research Centre
CanROC: Canadian Resuscitation Outcomes Consortium
CI: Confidence Interval
CPR: Cardiopulmonary Resuscitation
FTP: File Transfer Protocol
ITS: Interrupted Time Series
OHCA: Out-of-hospital Cardiac Arrest
OHRI: Ottawa Hospital Research Institute
ROC: Resuscitation Outcomes Consortium
